### Outcome measurements and definitions

The primary outcome of the study will be the incidence of PEP, defined as abdominal pain consistent with acute pancreatitis and an elevation greater than three times the upper limit of normal of serum lipase levels [23].The secondary outcomes of the study include:
Rate of successful cannulation of the CBD, with technical success determined by a cholangiogram;Inspection time; defined as time from visualization of ampulla to appearance of needle knife or sphincterotome;Time to successful cannulation, measured as follows:
i.Standard cannulation group (group I): time of endoscopic visualization of the sphincterotome on the screen to contact with the papilla orifice;ii.NKF group (group II): time of endoscopic visualization of the metal point of the needle knife on the screen to successful CBD cannulation as evident by the cholangiogram or wire advancement into the CBD;Total procedure time, measured for completed procedures from the time of esophageal intubation to the time of scope withdrawal from the patient mouth,Ampullary morphology—cannulation success and pancreatitis ratesDifficulty of cannulation, graded on a 3-point scale, based on the operator’s subjective opinion (easy, moderately difficult, very difficult), and,Incidence of complications graded and defined by Cotton et al. [20], notably, intra-procedural bleeding that required intervention (cautery, clips, or injection of epinephrine), delayed or sustained bleeding requiring transfusion or repeat endoscopy and immediate or delayed perforation.

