### Initial data collection and data management

Pre-procedure demographics, as well as lab results of liver enzymes, total bilirubin, lipase, international normalized ratio (INR), hemoglobin, platelets, and the white blood cell count will be recorded. The physician will document any abdominal pain and/or tenderness, both for severity and location. The suspected diagnosis will be documented along with radiologic findings.

Intra-procedure data collection will include total sedation used, sedation start time, endoscope insertion time, visualization of the ampulla, visualization of needle knife or sphincterotome on the screen, time of the sphincterotome making contact with papilla orifice, time of successful cannulation of the bile duct, time for remaining interventions, time of scope out of mouth, and administration of diclofenac. Each procedure will be recorded for verification purposes.

Other data recorded includes the following: ampullary morphology, difficulty of cannulation, normality/abnormality of the CBD, CBD stent placement, cannulation of the pancreas, pancreatic stent placement, pancreatic contrast injection, and any intraprocedural complications.

Post-procedure data will include assessment for pain/ pancreatitis at 24 h post-procedure. If the subject is an inpatient, this will include clinical assessment. If the subject is an out-patient, then they will be contacted by phone and questioned regarding abdominal pain. Should the subject report abdominal pain consistent with pancreatitis, they will be advised to come to the nearest emergency room for assessment as per current standard of care. A post-procedure day 7 phone call will also be scheduled, and subjects will be questioned regarding abdominal pain. Any post-procedure complications will be recorded as previously outlined. Outcome assessors will not be blinded to the treatment group.

Data will be inputted electronically by a full-time research assistant and stored and managed on a secure encrypted program.

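### Time to successful cannulation stops at papilla contact in the standard arm but at bile duct cannulation in the NKF arm, so this secondary comparison is biased against NKF as written

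*Protocol article*

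**What the plan says.** Under Outcome measurements and definitions, the protocol article introduces the outcome with "Time to successful cannulation, measured as follows" and then gives one definition per arm.

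- Standard cannulation (group I): "time of endoscopic visualization of the sphincterotome on the screen to contact with the papilla orifice".
- NKF (group II): it starts at "time of endoscopic visualization of the metal point of the needle knife on the screen" and runs "to successful CBD cannulation as evident by the cholangiogram or wire advancement into the CBD".

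The same section defines the success outcome as "Rate of successful cannulation of the CBD, with technical success determined by a cholangiogram", with no distinction by arm.

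Under Initial data collection and data management, the list of intra-procedure times contains "time of the sphincterotome making contact with papilla orifice, time of successful cannulation of the bile duct". These are two separate items, and the second is not restricted to one arm. The appearance of either device on screen is also on the list, and each procedure is recorded for verification.

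Study design and setting says that the secondary outcomes serve to compare the safety and efficacy of the two methods. Statistics and sample size plans regression or two-sample tests for them.

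**The concern.** The two clocks start at matching events, the appearance of the allocated device on screen, but stop at different ones. In the standard arm the clock stops when the attempt begins; in the NKF arm it stops when the attempt has succeeded. One name covers two quantities, and the difference between them is not a difference in speed of access.

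Two things follow. First, the standard-arm figure leaves out the cannulation attempt itself. Second, the set of patients with a value differs between arms: every standard-arm patient whose papilla is touched has a time, whether or not the duct is ever entered, whereas an NKF patient without successful cannulation has no defined stop.

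At stake is an efficacy outcome that the abstract names. If the definition is applied literally, NKF can appear slower when the techniques are equally fast, and a true advantage for NKF in access time would be reduced, hidden or reversed.

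**Working it through.** **Step 1. Is contact the same event as cannulation in this protocol?** Three places say it is not.

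- Outcome measurements and definitions determines technical success by cholangiogram, which contact alone cannot supply.
- Procedure provides for switching approach when standard-arm cannulation has not been achieved in 10 min. Attempts can therefore last minutes after the device reaches the papilla.
- Initial data collection and data management lists papilla contact and "time of successful cannulation of the bile duct" as separate time stamps.

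Nothing elsewhere in the article corrects or overrides the standard-arm definition.

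**Step 2. Direction.** Procedure states that the standard arm gains access through the native orifice. Access by that route cannot precede contact with the orifice. For each standard-arm patient cannulated that way:

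recorded time = true time to cannulation − (time from contact to cannulation),

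and the bracket is never negative. The recorded NKF-minus-standard difference is therefore shifted against NKF, whatever the true times are.

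**Step 3. Size, by illustration.** The plan states no figure for this outcome, so there is none to reproduce. The only input taken from the documents is 269 patients per arm (Statistics and sample size). All other inputs are assumptions:

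- true mean time from device on screen to bile duct cannulation, equal in both arms: m = 2 to 5 min;
- mean time from device on screen to papilla contact: c = 0.3 to 0.5 min;
- SD of the NKF-arm time: 2 to 4 min;
- SD of the contact time: 0.3 min.

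False difference = m − c. Smallest: 2 − 0.5 = 1.5 min. Largest: 5 − 0.3 = 4.7 min.

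Standard error = √[(SD² + 0.3²)/269].

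- SD 2: √(4.09/269) = 0.123 min.
- SD 4: √(16.09/269) = 0.245 min.

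| m (min) | c (min) | False difference (min) | In SEs, SD 2 | In SEs, SD 4 |
|---|---|---|---|---|
| 2 | 0.5 | 1.5 | 12.2 | 6.1 |
| 2 | 0.3 | 1.7 | 13.8 | 7.0 |
| 5 | 0.5 | 4.5 | 36.5 | 18.4 |
| 5 | 0.3 | 4.7 | 38.1 | 19.2 |

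The range is about 6 to 38 standard errors.

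**Step 4. Check with skewed times.** A simulation with 269 per arm drew identical log-normal cannulation times in both arms (median 2, 4 or 6 min, log SD 0.8) and a median contact time of 0.1, 0.25 or 0.5 min (log SD 0.5, capped at the cannulation time). These values are also assumptions. There were 200 runs for each of the nine combinations.

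- Definition as written: average difference in medians of 1.51 to 5.90 min against NKF. The Mann-Whitney test was significant at 0.05 in every run.
- Common stop at cannulation: average difference in medians between −0.04 and 0.01 min, so the false difference disappears.

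**The case against.** **It is probably a drafting slip.** Stopping at contact contradicts the outcome's own name, and the data list collects the cannulation time without restriction by arm. An analyst might well use the correct stamp. This is plausible, and it means that a false finding of slower NKF is conditional on the printed definition being followed. But no text says it is a slip, the contact time is collected as its own item, which fits its use in this definition, and the definition is explicit. The printed rule needs correcting either way.

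**A fuller analysis plan may settle it.** That would answer an omission. Here the article states a definition, and the definition is wrong as stated.

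**Other outcomes cover the question.** Total procedure time has the same start and stop in both arms and gives a fair comparison of overall duration. It also includes stone removal, stenting and other interventions, so it does not isolate access time. The point stands for this outcome, but it does limit the consequence.

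**The mismatch between wire advancement and cholangiogram.** A reader might infer that the NKF stop event is itself faulty, because technical success rests on a cholangiogram alone, and that only a cholangiogram would do. The documents do not support this. Procedure treats guidewire advancement and contrast injection as steps of one confirmation, and either event removes the asymmetry if it is used in both arms.

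**Wider damage.** A reader might also infer that the trial's main conclusion is compromised. It is not: post-ERCP pancreatitis, the sample size, the cannulation success rate and the stopping criteria under Safety reporting do not use this interval.

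**Conclusion.** The point holds for one secondary outcome. As written, time to successful cannulation measures different things in the two arms, and the comparison is biased against NKF. The direction rests only on contact preceding access through the orifice, so it needs no numerical assumption.

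The size does rest on assumptions, because the documents contain no cannulation times. Under equal true means of 2 to 5 min and the other values above, the false difference is about 1.5 to 4.7 min, or 6 to 38 standard errors. Even the low end would be declared significant. These figures show that 269 per arm is enough to turn the definitional gap into a firm but false result; they do not predict what the trial will find. If NKF is truly faster to access, the same shift would shrink or reverse that advantage.

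The definition should be corrected before this outcome is analysed.

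**What to change.** Replace the two arm-specific definitions with one: from first appearance of the allocated device on screen to successful bile duct cannulation, confirmed by the same event in both arms. The confirmation already written for NKF, cholangiogram or wire advancement, would serve; so would cholangiogram alone, if applied to both.

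State one analysis rule, identical in both arms, for patients whose cannulation fails or whose approach is switched: whether the clock continues after a switch, and what value or censoring applies when the duct is never entered. This concerns the derivation of the variable only and leaves the clinical switching criteria as they are.

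If the interval from device to papilla contact is of interest, report it separately under its own name as a descriptive measure.

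The cost is a wording change and one derived variable. Device appearance and bile duct cannulation times are already on the data collection list, so no new data or patients are needed, and patients already enrolled can be re-derived, with the procedure recordings available for checking.

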### Procedure

After obtaining consent, baseline patient characteristics (age, sex, indication for ERCP, preprocedure blood work including ALP, bilirubin, INR, hemoglobin and lipase) and the suspected diagnosis will be documented. The ERCP procedure will follow standard practice for patient preparation, sedation, and intubation of the duodenum. Patients will not be blinded to their treatment group. Patients will receive sedation in the form of midazolam, diazepam, fentanyl, and/or dimenhydrinate. Diclofenac will be administered per rectum at the conclusion of the procedure.

Access to the CBD will be attempted via either NKF or a standard sphincterotome. Upon identification of the ampulla, the operator will evaluate the feasibility of performing both the needle-knife fistulotomy and standard cannulation. If both approaches are feasible, then participants will be randomized with a 1:1 allocation to one of two treatment groups using a central online randomization program (Randomizer for Clinical Trials app, Medsharing, France) and block randomization. The block sizes will not be disclosed to ensure concealment. Should the operator determine that they are unable to safely perform one of the approaches, then the participant will not be randomized. Allocation concealment will be ensured, as the online randomization program will not reveal the treatment group until the endoscopist confirms both approaches are feasible.

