To perform the NKF, the ampulla will be identified and closely examined to accurately delineate the infundibulum. A needle knife (Needlecut 3 V, Olympus Medical Canada, Markham, Ontario) will be used to make a 2–3-mm incision in the mid to proximal third of the vertical axis in the intra-duodenal segment of the bile duct. The needle will be used to cut through the mucosa with intermittent examination for the muscular ampullary complex and subsequent penetration into the bile duct usually signaled by bile flow. When bile is seen, the fistula will be gently probed with a guidewire until the CBD is cannulated. Cannulation of the CBD will be confirmed with proximal advancement of the guidewire and contrast injection with cholangiography. If the findings on the cholangiogram indicate that further interventions are necessary, then the fistulotomy site will be extended with the use of standard sphincterotome or balloon sphincteroplasty as per operator. Further interventions include placement of metal or plastic biliary stents, brushing of the ducts for cytology, balloon dilation of strictures, intraductal cholangioscopy basket retrieval of stones, and balloon sweeping of the CBD.

The standard cannulation will be performed using a traditional sphincterotome (Clever-cut 3 V, Olympus Medical Canada, Markham, Ontario) with access gained to the biliary system via the native orifice (group I).

The operator will switch approaches under the following circumstances: [1] the patient was randomized to the sphincterotomy group (group I), but cannulation is not achieved in 10 min or [2] the patient was randomized to the NKF group (group II), but the operator is unable to achieve biliary access and feels they cannot safely cut further.

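### Secondary time outcomes do not compare the randomised arms like for like: total procedure time is limited to undefined completed procedures, and the cannulation clock stops at different events in the two arms

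*Protocol article*

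**What the plan says.** Three secondary outcomes in the protocol article (Methods, Outcome measurements and definitions) are durations.

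- **Total procedure time:** "Total procedure time, measured for completed procedures", with the clock running from oesophageal intubation to scope withdrawal. The word completed is not defined.
- **Time to successful cannulation:** each arm has its own definition. For the standard arm (group I) it is "time of endoscopic visualization of the sphincterotome on the screen to contact with the papilla orifice". For the NKF arm (group II) the clock starts when the needle tip is seen and runs "to successful CBD cannulation as evident by the cholangiogram or wire advancement into the CBD".
- **Inspection time:** "time from visualization of ampulla to appearance of needle knife or sphincterotome".

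The Procedure section gives the order of events: "Upon identification of the ampulla, the operator will evaluate the feasibility of performing both the needle-knife fistulotomy and standard cannulation". The allocation is revealed only after both approaches are confirmed feasible. The same section has a switch rule for each arm. The rule for the standard arm is timed ("the patient was randomized to the sphincterotomy group (group I), but cannulation is not achieved in 10 min"); the rule for the NKF arm rests on the operator's judgement and has no time limit.

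Under Statistics and sample size, intention to treat is stated for the primary outcome. Secondary outcomes get regression, linear where appropriate, with a t-test or the Mann-Whitney-Wilcoxon test according to distribution. The data collection section already lists endoscope insertion, device appearance, papilla contact, successful bile duct cannulation and scope-out as recorded times.

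**The concern.** The article says that the secondary outcomes will further compare the safety and efficacy of the two methods, so readers will take a difference in procedure or cannulation time as an effect of the technique. Three features of the definitions stand in the way.

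1. Restricting total time to completed procedures conditions on something that happens after randomisation and that the technique may influence. Randomisation no longer protects the comparison if completion differs between arms.
2. One outcome name covers two different intervals. The standard-arm interval ends when the device touches the papilla, before the duct has been entered. The NKF interval ends when the duct has been entered. The difference between arms then partly reflects the definition.
3. Inspection time includes the feasibility check and the randomisation step, neither of which is a property of the technique.

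At stake is the credibility of the efficiency claims, not of the pancreatitis result.

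**Working it through.** **The plan's own figure.** The article gives no figure for any time outcome. Its only calculation is 538 patients for the primary outcome. With 7% against 2%, two-sided alpha of 5% (the article prints 0.05%) and 80% power:

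n per arm = [1.960 × √(2 × 0.045 × 0.955) + 0.842 × √(0.07 × 0.93 + 0.02 × 0.98)]² / 0.05² = (0.5746 + 0.2449)² / 0.0025 = 268.7, so 269 per arm and 538 in all.

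This reproduces the plan, and nothing below changes it.

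**Order of the clock points**, from the outcome definitions and the Procedure section:

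| Event | Clock |
|---|---|
| Oesophageal intubation | total time starts |
| Ampulla seen | inspection time starts |
| Feasibility check, then allocation revealed | none |
| Device appears | inspection time ends; cannulation time starts |
| Papilla contact | cannulation time ends, standard arm |
| Bile duct cannulated | cannulation time ends, NKF arm |
| Scope out | total time ends |

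**Cannulation time.** In the standard arm, let a be the time from device appearance to papilla contact and b the time from contact to duct access. The full time to access is T = a + b. In the NKF arm the full time T′ is recorded. The planned contrast is a − T′ = (T − T′) − b. It therefore differs from the like-for-like contrast by the mean of b, always in the direction that makes the standard arm look faster. The article gives no value for b. It does list papilla contact and successful cannulation as separate recorded times, so it treats them as different events. A standard-arm failure still has a value, because contact does not require success. An NKF failure has none.

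**Total procedure time, illustration only.** Assume lognormal times with median 30 min and log-SD 0.5, the same in both arms, so the true difference is zero. The full mean is 30 × exp(0.5²/2) = 34.0 min. Remove a fraction f from one arm only, with z the (1 − f) normal quantile:

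- longest removed: mean = 34.0 × Φ(z − 0.5)/(1 − f)
- shortest removed: mean = 34.0 × Φ(z + 0.5)/(1 − f)

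| f | of 269 | Mean, longest removed | Shift | Mean, shortest removed | Shift |
|---|---|---|---|---|---|
| 5% | about 13 | 31.3 | −2.7 | 35.2 | +1.2 |
| 10% | about 27 | 29.6 | −4.4 | 36.4 | +2.4 |
| 20% | about 54 | 26.9 | −7.1 | 38.7 | +4.7 |

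These are extreme cases, since removal is one-sided and perfectly sorted by duration. They show that the restriction can create a difference of minutes and that its sign depends on which procedures count as not completed. The fractions are assumptions, not rates from the article.

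**Inspection time, illustration only.** Assume exponential segments: before allocation, mean 60 s in both arms; after allocation, means 20 s and 30 s. The expected difference is (60 + 30) − (60 + 20) = 10 s, the same as from allocation onwards. The standard error is √[(60² + 20² + 60² + 30²)/269] = √(8500/269) = 5.6 s, against √[(20² + 30²)/269] = √(1300/269) = 2.2 s when timed from allocation. Precision is lost, but no bias arises.

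**The case against.** The other side has good arguments, and they limit the point.

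- **Completed is undefined.** A patient whose first technique fails is switched to the other, and if access follows the procedure is completed. Few patients, or none, may be excluded. This stands: selective loss is a risk created by the wording, not an established fact. But if every procedure counted as completed, the qualifier would do no work.
- **Failures are visible elsewhere.** Cannulation success is its own outcome and the number of switches will be reported. This stands, but it does not repair a time comparison.
- **Detail may sit in an analysis plan.** Rules for failed or switched patients commonly do. That covers the missing rule for NKF failures. It does not cover the unequal clock ends or the restriction, both of which the article states itself.

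A reader might also infer four stronger things that the article does not support.

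1. *Cannulation time drops failures in both arms and is cut at 10 min in the standard arm.* The standard-arm clock stops at papilla contact, which needs no success and would normally come before any switch.
2. *Inspection time is mostly a pre-allocation interval and cannot differ by arm.* No segment durations are given. The interval ends when the allocated device appears, so it spans allocation. Its earlier part is balanced in expectation among randomised patients.
3. *The 5 to 10% failure of standard access in the Background, or 13 to 27 of 269 patients, counts patients lost from total time.* That rate describes first-technique access, after which another technique follows. It is not a non-completion rate.
4. *The arm with more failures will look faster.* An abandoned procedure skips stone, stent and brushing work and may be short, so the sign is open.

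**Conclusion.** The point holds for secondary outcomes only, in three parts of unequal weight.

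- **Cannulation time:** certain from the text. The arms stop the clock at different events, so the comparison is invalid as defined. It favours the standard arm by the mean time from contact to access, a quantity that the article does not give.
- **Total procedure time:** conditional. Restricting to an undefined post-randomisation status may break the randomised comparison. Neither direction nor size can be read from the article; the shifts of a few minutes shown above rest wholly on assumed times and exclusion fractions.
- **Inspection time:** minor. It loses precision and is harder to interpret, but it is not biased.

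The pancreatitis analysis and the 538 patients are untouched. The change is worth making because the needed times are nearly all recorded already.

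**What to change.** - **Total procedure time:** report it for every randomised patient in the arm assigned, from insertion to scope-out, both of which are already collected. Define completed and keep the completed-only comparison as supplementary.
- **Time to bile duct access:** use one definition in both arms, from appearance of the allocated device to successful bile duct cannulation, counted through any switch. Rank failures worst in the Mann-Whitney test already planned, or censor them in a time-to-event analysis, and state which in advance. Appearance to papilla contact can stay as a separate descriptive interval for the standard arm.
- **Inspection time:** start it when the allocation is revealed, if the online randomisation system supplies a timestamp. The data collection section does not list one, so this must be confirmed. Otherwise label the outcome descriptive.

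The cost is a change of wording and, at most, one extra timestamp. Medians or time-to-event summaries would replace means as the main summary of time to access. No change to sample size, treatment or switch rules is needed.
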